##### 7.1.5 End of the Study

- At 3 years post-implantation, the subject completes the protocol observation period, and the ILR is explanted.
- If an adverse event or device malfunction (e.g., battery depletion) necessitates explantation, the study observation ends at that time.
- If a new device (e.g., a permanent pacemaker) is implanted, rendering ILR monitoring moot, ILR is explanted, and observation ends.
- If follow-up is no longer feasible, the ILR is explanted, and observation ends.
- Explantation is generally performed on an outpatient basis with local anesthesia. The removed ILR is discarded per institutional procedures.
- The MyCareLink Relay Home Communicator is discarded as non-burnable trash.

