### **5. Details of the Clinical Research**

#### 5.1 Primary and Secondary Endpoints

#### (See “8. Evaluation of Efficacy” for details.) The primary analysis will use data at 1 year post-implantation; after all patients have completed the 3-year follow-up, a final analysis will be performed.

- **Primary Endpoint**
  Proportion of patients in whom AF or non-sustained or sustained VT is detected

Definition: Among the analysis population, the percentage of patients with any of:

- - AF lasting ≥6 minutes
  - Non-sustained VT: heart rate >150 bpm, ≥16 consecutive beats, ≤30 s
  - Sustained VT: heart rate >150 bpm, lasting ≥30 s

Rationale: These arrhythmias would clinically warrant consideration of intervention (pharmacological, ablation, or device-based).

- **Secondary Endpoints**
  - Proportion of patients with pauses ≥4.5 seconds
  - Proportion of patients with bradycardia <30 bpm
  - Proportion of patients with high-grade AV block
  - Proportion of patients receiving permanent pacemakers, ICDs, catheter ablation, or antiarrhythmic drug therapy
  - All-cause mortality
  - Cardiovascular mortality
  - Proportion of patients requiring hospitalization for cardiovascular disease or heart failure
  - Proportion of patients experiencing stroke

Rationale:

- - (1)–(3): They may require consideration of therapeutic intervention.
  - (4): To evaluate the effect of continuous ECG monitoring by ILR on treatment decisions.
  - (5)–(8): To evaluate the relationship between ILR findings and clinical outcomes.
- **Safety Evaluation Items**
  - Incidence of adverse events related to ILR implantation
  - Incidence of malfunctions

(Rationale: General safety assessment items.)

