##### 7.1.4 Outpatient Follow-up

- The patient continues outpatient visits every 1–3 months. During those visits, events related to secondary endpoints 4–8 and the subject’s clinical status are confirmed.
- Additional tests may be performed as necessary for standard care.
- No extra examinations are performed solely for this study.
- If the subject moves away, it may still be possible to continue in the study if certain conditions are met (e.g., medical records can be obtained from a local hospital, the subject agrees to return for ILR explantation unless physically impossible, etc.).

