##### 7.3.2 Prohibited

- Diathermy (radiofrequency, shortwave, microwave)
- Permanent pacemaker implantation
- ICD implantation

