#### 7.6 Discontinuation Criteria for Each Study Subject

1. Subject withdraws consent.
2. ILR cannot be implanted within 30 days of registration.
3. Study continuation deemed difficult by PI or sub-investigator due to worsening primary disease or severe AEs.
4. ILR explantation due to AE or malfunction.
5. Need for another CIED (e.g., permanent pacemaker), leading to ILR explant.
6. Follow-up no longer feasible due to relocation, etc., leading to explant.
7. Prohibited therapy is required or has been administered.
8. Serious deviations from the Clinical Trials Act or from the protocol.
9. Inability to adhere to the protocol.
10. Pregnancy.
11. Entire study is discontinued.
12. Other reasons deemed appropriate by the investigator.

If any discontinuation occurs, reasons and details are documented, and the subject is followed clinically as appropriate.

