##### 8.1.2 Secondary Endpoints

1. Proportion of patients with pauses ≥4.5 s
2. Proportion of patients with bradycardia <30 bpm
3. Proportion of patients with high-grade AV block
4. Proportion of patients receiving pacemaker, ICD, ablation, or antiarrhythmic therapy
5. All-cause mortality
6. Cardiovascular mortality
7. Proportion with hospitalizations for CV disease/HF
8. Proportion who experienced stroke

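### A pacemaker or ICD implant is counted as a secondary endpoint, prohibited, and made the end of observation, with no requirement to collect death, hospitalisation or stroke afterwards

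*Protocol*

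**What the plan says.** Section 5.1 defines secondary endpoint 4 as "Proportion of patients receiving permanent pacemakers, ICDs, catheter ablation, or antiarrhythmic drug therapy", and 8.1.2 repeats it as "Proportion of patients receiving pacemaker, ICD, ablation, or antiarrhythmic therapy". The same section gives the purpose of endpoints 5–8: "To evaluate the relationship between ILR findings and clinical outcomes". According to 7.1.4, the data for these endpoints come from outpatient visits every 1–3 months: "During those visits, events related to secondary endpoints 4–8" are confirmed there, along with clinical status.

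Section 7.3.2 lists "Permanent pacemaker implantation" and ICD implantation among prohibited therapies and states no exception for clinical need. Section 7.6 discontinues a patient who needs another implanted cardiac device (item 5), and also when "Prohibited therapy is required or has been administered" (item 7). Section 7.1.5 adds: "If a new device (e.g., a permanent pacemaker) is implanted, rendering ILR monitoring moot, ILR is explanted, and observation ends".

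For the time after discontinuation, 7.6 says: "If any discontinuation occurs, reasons and details are documented, and the subject is followed clinically as appropriate". Section 11 treats the course after discontinuation as data for which the CRF is the source.

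**The concern.** There are two problems.

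The first is a contradiction. One clinical act is a planned endpoint event, a prohibited therapy and a reason for discontinuation. Section 23 gives prohibited concomitant therapies as an example of serious non-compliance, which must be reported to the review board. Implants are foreseeable: Section 3 says high-risk HFrEF cases may need an ICD, and 5.1 justifies the primary endpoint partly because the arrhythmias may call for device-based intervention.

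The second matters more for the estimates. Ending observation at implant removes later deaths, hospitalisations and strokes from the data. Patients who receive a device are probably not a random subset, and some will receive it because of what the ILR showed. The stop is therefore plausibly informative for exactly the relationship endpoints 5–8 are meant to describe. A later analysis plan cannot recover outcomes that were never collected.

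**Working it through.** **Text check: does anything require endpoints 5–8 after a device implant?**

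- 7.1.5 ends observation at the implant.
- 7.6 offers clinical follow-up but names no endpoint, schedule or duration.
- Section 11 says where post-discontinuation data would be sourced, not that they must be collected.
- 5.6 extends follow-up only for adverse events suspected to be study-related.
- 9.2 sets a three-year window for safety endpoints only.
- 10.3 applies last observation carried forward to patients lost to follow-up. That is an analysis rule; applied here, it would carry an event-free status forward.
- 10.6 places the final analysis after all patients complete three years, which device recipients cannot do under 7.1.5.

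No section contains the requirement.

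**Size without a model.** If *k* of 35 patients are cut short, worst-case bounds on any endpoint 5–8 proportion widen by up to *k*/35: 2/35 = 5.7 points, 4/35 = 11.4 points, 7/35 = 20.0 points.

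**Size with a model (illustration only).** The protocol gives no event rate or implant rate, so every input except the 35 patients and 3 years is assumed:

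- base 3-year event risk 35%, so λ = −ln(0.65)/3 = 0.1436 per year;
- a share *p* of 15% or 25% destined for a device, with hazard 2λ;
- implant time uniform over 0–3 years, with observation ending at implant.

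The share implanted before an event is p·(1 − e^(−6λ))/(6λ), which is 10.1% and 16.8%.

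*True 3-year risk.* (1 − p)·0.35 + p·(1 − 0.65²). Recipients' true risk is 1 − 0.65² = 57.8%.

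*Crude recorded risk.* Recipients contribute only events before implant: 1 − (1 − e^(−6λ))/(6λ) = 33.0%. Overall this is (1 − p)·0.35 + p·0.330.

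*Kaplan-Meier censored at implant.* With a(t) = (1 − p)e^(−λt) and b(t) = p·e^(−2λt)(1 − t/3), the hazard among those still observed is h(t) = λ(a + 2b)/(a + b). The limit is 1 − exp(−∫h dt) over 0–3 years.

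| 3-year result | p = 15% | p = 25% |
|---|---|---|
| True | 38.4% | 40.7% |
| Crude recorded | 34.7% | 34.5% |
| Crude gap | 3.7 points (1.3 of 35) | 6.2 points (2.2 of 35) |
| Kaplan-Meier | 36.9% | 38.3% |
| Kaplan-Meier gap | 1.5 points (0.5 of 35) | 2.4 points (0.8 of 35) |

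At 1 year the gaps are 0.6–1.0 points (crude) and 0.2–0.4 points (Kaplan-Meier).

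**Sensitivity: the device helps.** Let the hazard be 2λ before implant and 0.7λ after. Recipients' true risk becomes 1 − e^(−2.1λ)·(1 − e^(−3.9λ))/(3.9λ) = 43.4%, and the overall true risk is 36.25% and 37.09%. The recorded figures do not change. Crude is too low by 36.25 − 34.70 = 1.6 and 37.09 − 34.49 = 2.6 points. Kaplan-Meier is too high by 36.91 − 36.25 = 0.7 and 38.29 − 37.09 = 1.2 points.

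**Wider range of inputs.** With 5–30% receiving a device, 3-year risk 20–40% and a hazard ratio of 1–2, the crude understatement runs from 0.5 to 8.0 points. If recipients lose 1.5 years each on average, lost follow-up runs from 35 × 0.05 × 1.5 = 2.6 to 35 × 0.30 × 1.5 = 15.8 of the planned 35 × 3 = 105 person-years.

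**The case against.** - **The prohibition changes little in practice.** Sections 7.1.5 and 7.6 foresee an implant and say what to do, and 7.2.2 records it with its date. Care is not denied and the endpoint-4 implant can be counted. This stands. What remains is an inconsistent label, a possible non-compliance report, and the loss of any ablation or antiarrhythmic therapy started after the implant.
- **Observation was designed to last as long as the ILR.** Section 3 ties the three years to battery life, and post-discontinuation data are left unspecified rather than ruled out. It is true that collection is not forbidden. But nothing requires it, the explicit words say observation ends, and battery life is no reason to stop recording deaths or strokes.
- **The stop is not confined to device recipients.** Section 7.1.5 also ends observation after explant for an adverse event or malfunction, and when follow-up is infeasible. Correct. The device trigger is the one most likely to be informative, and the fix below covers every explant.
- **The effect is small.** All model inputs are assumed, and one 35% risk stands in for four endpoints. With a 5% base risk the crude 3-year gap is only about 0.7–1.2 points; with 10%, about 1.4–2.3. If the device is implanted during a cardiovascular admission, that admission may itself count for endpoint 7. At 35 patients and a proportion near 38%, the 95% interval is roughly 1.96·√(0.38 × 0.62/35) = ±16 points, wider than any gap shown. All of this is fair and limits the severity. It does not justify adding an avoidable bias to an already imprecise estimate.

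**Conclusion.** The concern holds, as something that should be fixed rather than a threat to the study. A pacemaker or ICD implant is at once an endpoint event, a prohibited therapy and the end of observation, and the protocol does not require endpoints 5–8 to be collected afterwards. This rests on the text and needs no assumption.

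The size is illustrative only. Under the main assumptions, a crude 3-year proportion loses about one to two of 35 patients' events, and a Kaplan-Meier estimate less than one. The Kaplan-Meier error can go either way, so choosing that method does not reliably cure it. Rarer endpoints and the 1-year main analysis are affected less. The primary endpoint and the count of implants in endpoint 4 are largely unaffected, and the study is exploratory with a single arm.

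**What to change.** 1. In 7.3.2, remove clinically indicated pacemaker and ICD implantation from the prohibited list, so that item 7 of 7.6 no longer applies to it.
2. In 7.1.5 and 7.6, state that explant for any reason ends only ILR assessment, meaning the primary endpoint and secondary endpoints 1–3.
3. State that endpoints 4–8 continue to be collected to 36 months after implantation of the ILR from the routine 1–3-monthly visits, unless consent is withdrawn or follow-up is not feasible.
4. State that an implant counted under endpoint 4 is not in itself a protocol deviation.

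The cost is a protocol amendment, matching consent wording and continued data entry after explant. No visits or tests are added, because the data come from routine care.

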#### 7.2 Observation/Examination Items and Schedule

##### 7.2.1 Schedule

| **Observation Items** | **Pre-Implant** | **At Implant** | **Remote Monitoring After Implant** |
| --- | --- | --- | --- |
| Informed Consent (IC) | ● |  |  |
| Registration | ● |  |  |
| Subject Background Info | ● |  |  |
| ILR Implantation |  | ● |  |
| Remote Monitoring: arrhythmia events¹ |  |  | 6/12/18/24/30/36 months ±4 weeks |
| 12-lead ECG² | ● | ● |  |
| Echo (LAD, LVDd, LVDs, LVEF, etc.) | ● |  |  |
| Blood test (BNP) | ● |  |  |
| Chest X-ray | ● |  |  |
| Clinical course (every 1–3 months) |  |  | (Ongoing in standard outpatient care) |
| Adverse events, device malfunctions | (Monitored throughout the study) |  |  |

¹ ILR data are evaluated at 6-month intervals (±4 weeks).
² Baseline ECG: can be a monitor ECG at implant.

##### 7.2.2 Observation/Examination Items

1. **Informed Consent**
   Date of written informed consent
2. **Subject Background**
   - **Basic info**: DOB, age, sex, height, weight, BMI
   - **Comorbidities**: HF, hypertension, diabetes, stroke/TIA (for CHADS2), vascular disease (for CHA2DS2-VASc)
   - **Dialysis**: presence or absence
   - **Past cardiac surgery**: type, date
   - **Hospitalization history for HF**: presence, number of admissions, most recent admission date
   - **Current medications**: antiplatelet/anticoagulants, diuretics, beta-blockers, RAA inhibitors, MRAs, SGLT2 inhibitors, other HF therapies, antiarrhythmics
3. **Pre-implantation (Registration) Tests**
   - **Echocardiogram**: LAD, LVDd, LVDs, LVEF, IVS, LVPW, etc.
   - **Blood test**: BNP
   - **ECG**: 12-lead ECG to confirm rhythm (sinus, AF/flutter, paced, etc.)
   - **Chest X-ray**: cardio-thoracic ratio (CTR)
4. **At Implantation**
   - **ECG**: Monitor ECG (or 12-lead if possible) to confirm rhythm
5. **ILR Remote Monitoring**
   - Date of evaluation, evaluator
   - **AF ≥6 minutes**: presence/absence, date/time, number of events, total duration, etc.
   - **Non-sustained VT** (HR >150, ≥16 beats, ≤30 s)
   - **Sustained VT** (HR >150, ≥30 s)
   - **Pauses ≥4.5 s**
   - **Bradycardia <30 bpm**
   - **High-grade AV block**
6. **Clinical Course**
   - Mortality (date, CV or non-CV, details)
   - CV or HF hospitalizations (date, details)
   - Stroke (date, details)
   - Implantation of a permanent pacemaker, ICD therapy, catheter ablation, AAD therapy (dates, details)
7. **Adverse Events**
   - Onset date, resolution date, severity (Grade), treatment, outcome, seriousness, relationship to ILR, whether ILR explanted, etc.
8. **Device Malfunctions**
   - Malfunction name, onset/end date, presence of adverse event, whether ILR explanted, etc.

#### 7.3 Regulations on Concomitant Medications (Therapies)

##### 7.3.1 Permissible/Restricted

MRI scans should follow the device labeling conditions.

##### 7.3.2 Prohibited

- Diathermy (radiofrequency, shortwave, microwave)
- Permanent pacemaker implantation
- ICD implantation

#### 7.4 Instructions to Study Subjects

Before starting the study, the principal/sub-investigator instructs subjects to:

1. Inform any other doctors/hospitals that they are participating in this study and ideally consult the study physician in advance if other treatment is needed.
2. Report any health concerns promptly.
3. Notify their physician in advance if MRI is needed.
4. Avoid the use of high-frequency, shortwave, or microwave diathermy devices.
5. Follow the physician’s guidance regarding diet, exercise, etc.
6. Refrain from posting study-related information on social media, etc.
7. Notify the investigator immediately if pregnancy occurs.
8. Adhere to prohibited/restricted drug/therapy guidelines.

#### 7.5 Post-Study Arrangements

After study completion, subjects will receive the best possible prevention, diagnosis, or treatment options informed by the study results. If a subject wishes to continue ILR monitoring beyond the 3-year protocol period, the original ILR will be explanted, and a new one may be implanted under self-pay.

#### 7.6 Discontinuation Criteria for Each Study Subject

1. Subject withdraws consent.
2. ILR cannot be implanted within 30 days of registration.
3. Study continuation deemed difficult by PI or sub-investigator due to worsening primary disease or severe AEs.
4. ILR explantation due to AE or malfunction.
5. Need for another CIED (e.g., permanent pacemaker), leading to ILR explant.
6. Follow-up no longer feasible due to relocation, etc., leading to explant.
7. Prohibited therapy is required or has been administered.
8. Serious deviations from the Clinical Trials Act or from the protocol.
9. Inability to adhere to the protocol.
10. Pregnancy.
11. Entire study is discontinued.
12. Other reasons deemed appropriate by the investigator.

If any discontinuation occurs, reasons and details are documented, and the subject is followed clinically as appropriate.

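### Pacemaker and ICD implantation are prohibited therapies and also counted outcomes, and one stopping rule can take the subject out before the implant

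*Protocol*

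**What the plan says.** Four parts of the protocol bear on the same event.

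- **Prohibited list (Section 7.3.2).** Besides diathermy it names "Permanent pacemaker implantation" and "ICD implantation", without an exception for clinical need.
- **Endpoint 4 (Section 8.1.2, also Section 5.1 and the Overview).** It is the "Proportion of patients receiving pacemaker, ICD, ablation, or antiarrhythmic therapy". Section 5.1 gives its purpose: "To evaluate the effect of continuous ECG monitoring by ILR on treatment decisions".
- **Individual discontinuation (Section 7.6).** Item 7 stops a subject when "Prohibited therapy is required or has been administered". Item 5 is specific to devices: "Need for another CIED (e.g., permanent pacemaker), leading to ILR explant". The closing sentence of the section reads: "If any discontinuation occurs, reasons and details are documented, and the subject is followed clinically as appropriate".
- **End of observation (Section 7.1.5).** "If a new device (e.g., a permanent pacemaker) is implanted, rendering ILR monitoring moot, ILR is explanted, and observation ends".

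**The concern.** The protocol forbids a response to monitoring that it also expects and sets out to measure. Section 5.1 justifies the primary endpoint on the ground that the detected arrhythmias could call for drug, ablation or device treatment, and endpoint 4 then measures how often that treatment follows. Ablation and antiarrhythmic drugs, the other two components of endpoint 4, are not prohibited, so a single composite is governed by two different rules.

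The practical issue is timing. Item 7 of Section 7.6 can end participation at the moment a pacemaker or ICD is judged necessary. The implant, which is the endpoint event, would then come after exit, where the protocol promises only clinical follow-up as seen fit. The same device handled under Section 7.1.5 would be counted. Any resulting error goes one way: too few device treatments attributed to monitoring.

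**Working it through.** **Comparing the clauses.** Take a subject whose loop recorder shows an arrhythmia that calls for an ICD.

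1. The ICD is on the list in Section 7.3.2, so Section 7.6 item 7 applies. Its first limb is met on the date of need, and exit precedes the implant.
2. Under the second limb of item 7, exit follows the implant.
3. Under Section 7.1.5, observation ends when the new device is placed and the loop recorder removed. Exit coincides with the implant or follows it.
4. Section 7.6 item 5 starts from need but ties the stop to removal of the loop recorder, so it can be read consistently with Section 7.1.5. The conflict therefore lies in Section 7.3.2 combined with the first limb of item 7.
5. No clause gives item 5 or Section 7.1.5 priority over item 7, and none says whether an implant after exit counts for endpoint 4.

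**Would the implant still be recorded?** Probably. Section 7.2.2 item 6 collects dates and details of these devices, and Section 11 treats the course after discontinuation as case report form data. These provisions support recording without guaranteeing it after a stop for need.

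**Is treatment barred?** No. Section 22.1 makes adherence conditional on participants' safety and rights.

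**Size.** The protocol gives no expected device rate and no figure for endpoint 4, so there is nothing of its own to reproduce. The inputs are:

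- n = 35 (Section 10.2), assuming all 35 receive a loop recorder and so enter the full analysis set (Section 10.1).
- k = number of patients missed who had a device but neither ablation nor an antiarrhythmic drug. This is an assumption; 0 to 2 is shown.

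Reduction in endpoint 4 = k/35:

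- k = 0: 0 points
- k = 1: 1/35 = 2.86 points
- k = 2: 2/35 = 5.71 points

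Exact (Clopper-Pearson) 95% limits for x events in n are the 2.5% quantile of Beta(x, n − x + 1) and the 97.5% quantile of Beta(x + 1, n − x). The lower limit is 0 when x = 0. With one patient missed, for two assumed true counts:

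| True count | True result (95% CI) | Reported count | Reported result (95% CI) |
|---|---|---|---|
| 7/35 | 20.0% (8.44 to 36.94) | 6/35 | 17.1% (6.56 to 33.65) |
| 1/35 | 2.9% (0.07 to 14.92) | 0/35 | 0% (0 to 10.00) |

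In the first row the interval is 36.94 − 8.44 = 28.5 points wide, about ten times the 2.86-point shift.

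**The case against.** The strongest reply is that prohibition here works only as an exit rule, and a therapy can both end observation and be the subject's endpoint event. The device-specific clauses (Section 7.1.5 and Section 7.6 item 5) fit the case more naturally than the general item 7. Nothing in the protocol excludes events after discontinuation, a discontinued subject stays in the full analysis set, and the counting rule could sit in a statistical analysis plan that is not shown. To lose an event, the investigator would have to use item 7 rather than item 5, date the exit at need, and then fail to capture the implant. That last step is unlikely: the reason for stopping would itself be the device, and at a single centre that removes the loop recorder the implant would normally become known.

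Much of this stands. Loss of an event is possible, not shown; the missed counts are assumed; and zero is a credible value. What does not fall away is the contradiction itself. Item 7 applies as written, nothing subordinates it to item 5, and an analysis plan cannot change which procedures the protocol prohibits or when it discontinues a subject. The label also carries some weight elsewhere: Section 7.4 tells subjects to keep to the prohibited-therapy rules, and Section 23 gives breaches concerning prohibited therapies as an example of serious non-compliance. Whether an indicated implant followed by the prescribed discontinuation would be treated as such a breach is doubtful, and the point does not depend on it.

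**Conclusion.** The point holds and is minor. Followed literally, Section 7.3.2 with the first limb of Section 7.6 item 7 can place a subject's exit before an event that endpoint 4 is meant to count, while Section 7.1.5 places it at the implant. The likely effect on the estimate is nil to small: 0 to 5.7 percentage points for 0 to 2 missed patients, assuming 35 subjects in the denominator and missed patients who had neither ablation nor an antiarrhythmic drug. If every implant is taken from the case report form, the loss is zero. Neither the primary endpoint nor the ability to treat patients is affected.

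**What to change.** Reconcile the clauses in three short edits.

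1. **Section 7.3.2:** delete clinically indicated pacemaker and ICD implantation, leaving diathermy. Item 7 of Section 7.6 then no longer reaches them. This edit alone removes the conflict with item 7.
2. **Section 7.6 item 5:** change the trigger from the need for another device to the implantation of a permanent pacemaker or ICD with removal of the loop recorder, so that the exit date matches Section 7.1.5.
3. **Section 8.1.2:** state that such an implant counts under endpoint 4 if it occurs within 3 years of loop recorder implantation, or within 1 year for the main analysis.

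The cost is an amendment of a few sentences. The case report form already has the implant date field (Section 7.2.2 item 6), and no extra visits, tests or patients are needed.
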